### Baseline characteristics

The list of the baseline characteristics that we collect to evaluate the population:
GenderAgeHemorrhoid stageThe number of enlarged hemorrhoidsHemorrhoid symptoms

### The main outcome measures

The trial is conducted to evaluate the primary outcome: the quantity of the opioid administration intake per day during the first week postoperatively that is necessary to hold pain level no more than 3–4 VAS points in every patient. We use tramadol as an opioid analgesic in a single standard dose of 100 mg for patients with persistent severe pain syndrome in our clinic. The study also assesses the following secondary outcomes: (1) the pain severity before and after defecation according to VAS on the 6, 12, and 24 h after the procedure, then 2 times per day up to 7th postoperative day; (2) duration and (3) frequency of other analgesics intake (systemically and topically) during the first week postoperatively; (4) readmission rate and (5) overall quality of life on the 7th and 30th days; (6) time from the procedure to return to work; and (7) the complications rate (i.e. bleeding, retention of urine, infectious complications) in the early postoperative period (30 days after procedure). The pain severity, duration and frequency of other analgesics intake during the first week postoperatively will be assessed using “Postoperative protocol for pain management” (Additional file 2). The overall quality of life will be assessed with a patient-reported questionnaire Short Form 36 (SF-36). A total score in each of the 8 sections will be calculated and transformed into a 0–100 scale with a score of zero equivalents to maximum disability and a score of 100 equivalents to no disability. Other secondary outcomes will be updated during visits or by phone on the 7 and 30 days after the surgery.

All patients are scheduled to return to the ambulatory clinic on the 7 and 30 days after the surgery. During these visits, postoperative data is collected and digital rectal examination is performed. If a patient fails to follow up, the researcher may contact the patient by all means available (phone, email, or mail) to ascertain whether the patient has had any complications and/or adverse events that were treated at another hospital. If the researcher is unsuccessful in contacting the patient, the patient will be considered as lost to follow-up.

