### Sample size

Considering that this is a superiority study, the sample size was calculated using a 1-sided Blackwelder test. According to published data, the incidence of opioid intake after hemorrhoidectomy varies from 20 to 30% [7]. The expected incidence of opioid intake after hemorrhoidectomy with preemptive analgesia is not more than 10%. The purpose of this study is to show that the opioids intake in patients with preemptive analgesia is lower than without it. Considering that *a* = 0.05. the statistical power of the study is 80%, the patients are randomized into 2 groups with 1:1 allocation ratio, the noninferiority margin *D* = 5%, and the required sample size is 144 patients (72 patients in each of the 2 groups).

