### Statistics

The ITT analysis included all randomized patients treated for at least 1 week, who were evaluated for efficacy at baseline and at least once at subsequent evaluation points during the study. The PP-analysis will exclude from the full analysis all the non-compliant patients, patients who received incomplete treatment, and patients who refused further treatment after randomization.

Quantitative variables are described as means with standard deviations, medians, range, or interquartile range as appropriate. Categorical variables are described in absolute numbers and percentages. The statistical analysis of the quantitative variables, with independent groups, is performed with the parametric Student’s *t* test, providing that its conditions for application are met. Otherwise, the non-parametric Mann-Whitney *U* test is used. Statistical analysis for categorical variables is performed using the Pearson *χ*^2^ test or the Fisher exact test. Specifically, the above methods are used to compare the two groups in terms of baseline characteristics in order to assess whether the randomization has been effective. Ninety-five percent confidence intervals for the ratio will be reported. In all cases, the level of significance will be the usual 5% (*α* = 0.05).

This study has a low risk of selection bias due to the use of a computer random number generator. Central allocation and the use of sequentially numbered drug containers of identical appearance allow to achieve a low risk of deviations. Performance bias may be considered as having an average risk due to blinding only participants of the study, the personnel is not blinding. Blinding of outcome assessment is ensured, so detection bias is unlikely. Attrition bias could probably appear because of the difficulty of collecting data from patients outside the hospital or the refusal of future treatment and visiting the doctor during follow-up.

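### The stated primary outcome (opioid quantity per day) is not the variable the trial is sized on (incidence of opioid intake), so the 80% power belongs to a different endpoint and two primary analyses fit the text

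*Protocol article*

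**What the plan says.** Three sections of the protocol article bear on this.

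- **The main outcome measures** defines "the primary outcome: the quantity of the opioid administration intake per day during the first week postoperatively". It is an amount, and the unit is given too: "We use tramadol as an opioid analgesic in a single standard dose of 100 mg".
- **Sample size** works with a yes/no variable. For controls, "the incidence of opioid intake after hemorrhoidectomy varies from 20 to 30" per cent; for the ketoprofen arm, "The expected incidence of opioid intake after hemorrhoidectomy with preemptive analgesia is not more than 10" per cent. It adds that "the sample size was calculated using a 1-sided Blackwelder test", with alpha 0.05, 80% power and a 5% value for "the noninferiority margin", and arrives at 72 patients per arm.
- **Statistics** names no test for the primary outcome. It gives a rule by type of variable: "The statistical analysis of the quantitative variables, with independent groups, is performed with the parametric" t test if its conditions hold and the Mann-Whitney test if not, with chi-square or Fisher for categorical variables. It also says "Ninety-five percent confidence intervals for the ratio will be reported", without saying which ratio.

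**The concern.** A power statement applies to one variable, one test and one hypothesis. Here the defined variable is an amount, the sized variable is a proportion, and nothing in the article links them. No mean, standard deviation or expected difference in amount is given anywhere, so the 80% cannot be carried over to the outcome as defined.

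A reader following the outcome definition would run a t test or Mann-Whitney test on milligrams per day. A reader following the sample size section would compare the proportions using any opioid. These analyses have different effect measures and can disagree in the same data. Unless one is fixed beforehand, the choice could be made after the results are known. This is a conflict between statements in the article, not a detail left to a later document.

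**Working it through.** **Inputs.** Control incidence 20 to 30%, ketoprofen incidence 10%, D = 5%, alpha 0.05 one-sided, power 80%, 72 per arm (all from Sample size). The number of doses per user is not in the article and is assumed below.

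**1. Where 144 comes from.** Blackwelder: n per arm = (z_α + z_β)² × V / (Δ ± D)², with (1.645 + 0.842)² = 6.18.

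- 20% vs 10%, margin added to the difference, unpooled V = 0.20×0.80 + 0.10×0.90 = 0.25: 6.18 × 0.25 / 0.15² = 68.7, so 69 per arm, 138 in total.
- Same, pooled V = 2×0.15×0.85 = 0.255: 70.1, so 71 per arm, 142 in total.
- Superiority by more than 5 points (Δ − D), unpooled: 619, 172 and 83 per arm for control 20, 25 and 30%. None matches.
- Two-sided, no margin, 30% vs 10%, Fleiss formula with continuity correction: 72 per arm, 144 in total exactly, but this ignores the stated one side and margin.

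The article does not say which variant was used. Every route that reaches or approaches 144 compares proportions.

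**2. Sizing for the amount.** With no mean or SD, no sample size can be computed. In general, 72 per arm gives 80% two-sided power for a standardised difference of (1.96 + 0.842) × √(2/72) = 0.47. Nothing in the article says whether that is plausible.

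**3. What the amount would look like.** On the planning rates, 70 to 80% of controls and at least 90% of ketoprofen patients have an amount of zero. The expected median is 0 in both arms.

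**4. Cost of analysing the amount.** Simulation with 72 per arm, 10% users on ketoprofen, users taking 1 + Poisson(1) doses in both arms (assumed), 4000 trials, two-sided 5%:

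| Control incidence | Mann-Whitney on amount | t test on amount | Chi-square on any use |
|---|---|---|---|
| 20% | 39% | 33% | 39% |
| 25% | 66% | 57% | 68% |
| 30% | 86% | 77% | 87% |

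Mann-Whitney is within about 2 points of chi-square. The t test falls below Mann-Whitney by 39 − 33 = 6, 66 − 57 = 9 and 86 − 77 = 9 points. That loss depends on the dose assumption. With more variable dosing (geometric, mean 3.3 doses; 3000 trials) the t test has 26/44/65%, while Mann-Whitney stays at 39/67/86%.

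**5. The hypotheses differ.** With 20% users in both arms but users averaging 4 doses in one arm and 2 in the other, the t test rejects in about 36% of trials, Mann-Whitney in 6% and chi-square in 5%. A t test on the amount responds to dose among users; the sized comparison does not.

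**6. Power of 72 per arm for the proportion.** Power = Φ[(Δ − z × SE₀)/SE₁], with SE₀ pooled and SE₁ unpooled. For 25% vs 10%, two-sided: SE₀ = √(2×0.175×0.825/72) = 0.0633, SE₁ = √((0.1875 + 0.09)/72) = 0.0621, and (0.15 − 1.96×0.0633)/0.0621 = 0.42, giving 66%. All cases, no margin:

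| Control vs 10% | Two-sided 5% | One-sided 5% |
|---|---|---|
| 20% | 39% | 51% |
| 25% | 66% | 77% |
| 30% | 86% | 92% |

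**The case against.** The strongest reply is that the mismatch does little harm in practice. Statistics allows the t test only if its conditions are met. With most values at zero they would not be, so the plan leads to Mann-Whitney, which remains valid with many ties when corrected for them and has almost the power of chi-square. This stands, and it limits the size of the point. It does not remove the point: the article names no test for the primary outcome, and the power still refers to another variable.

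Three stronger readings are tempting, and the documents do not support them.

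- *That the mismatch is why power falls short of 80%.* Chi-square on any use falls short at 20 and 25% too. That shortfall comes from leaving the control rate as a range and from reading the test as two-sided. On the one-sided basis used for sizing, with the dose assumption of step 4, both tests on the amount exceed 80% at a control rate of 30% (Mann-Whitney 93%, t test 87%).
- *That the promised confidence interval cannot be produced for the primary outcome.* The ratio sentence stands in a general paragraph and is not tied to the primary outcome; it may concern binary secondary outcomes. It is vague, no more. Planning on a difference and also reporting a ratio is not in itself an error.
- *That a plain two-sided chi-square simply restores what was sized.* It does not: the sizing is one-sided and carries a 5% margin.

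It can also be said that the trial's aim, reducing opioid consumption, fits an amount at least as well as a yes/no outcome. That is fair. Choosing any use is a matter of convenience; the text does not dictate it.

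**Conclusion.** The point holds. The primary outcome is an amount per day, the sample size concerns an incidence, and the generic test rule sends the amount to tests other than the sized comparison. The stated 80% power therefore does not refer to the stated primary outcome, and two primary analyses fit the text. That conclusion rests on the article's wording alone.

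The power consequence is small for a rank test (about 2 points at most) and about 6 to 10 points for a t test. Both figures assume the same moderate dose distribution among users in both arms, and the t-test loss grows if dosing is more variable. The main harm is an open choice of confirmatory analysis. The low power at control rates of 20 to 25% is a separate matter.

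**What to change.** Before unblinding, amend the protocol and the registry record so that one primary variable appears in The main outcome measures, Sample size and Statistics.

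1. The simplest choice is any tramadol use to day 7 (yes/no). It is the only variable with planning figures, and it can be derived from the recorded amount, so no new data are needed. Compare the proportions by chi-square and report the risk difference with a 95% CI.
2. Keep the amount per day as a key secondary outcome: one value per patient for the week, a rank test, and the mean difference with a bootstrap CI.
3. In the same amendment, reconcile the one-sided test and the 5% margin in Sample size with the analysis. Restate the power of 72 per arm for the test chosen, without enrolling more patients. Two-sided and without a margin it is about 39%, 66% and 86% for control rates of 20%, 25% and 30% against 10%; one-sided at 5%, about 51%, 77% and 92%.
4. Name the effect measure that the ratio sentence refers to.

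The cost is one amendment and a registry update. Dose information moves from primary to secondary, and the stated power becomes less favourable unless the control rate is near 30%.

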## Methods

### Objective

The aim is to assess the efficacy of preemptive analgesia with Ketoprofen 100 mg 2 h before procedure per os with spinal anesthesia to decrease postoperative pain according to visual analog scale and to reduce the opioids and other analgesics consumption.

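### VAS pain is rated on about 15 occasions, up to 30 ratings per patient, but the plan fixes only a two-group test at 5% each time, so the pain question has no single error-controlled answer

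*Protocol article*

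**What the plan says.** The Objective section gives the aim as "to decrease postoperative pain according to visual analog scale and to reduce the opioids and other analgesics consumption", so pain comes first. The section on the main outcome measures makes opioid intake the primary outcome and lists pain as the first secondary one: "The study also assesses the following secondary outcomes: (1) the pain severity before and after defecation". The schedule is "the pain severity before and after defecation according to VAS on the 6, 12, and 24 h after the procedure", and "then 2 times per day up to 7th postoperative day".

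The Statistics section gives one rule for such data. "The statistical analysis of the quantitative variables, with independent groups, is performed with the parametric" Student's t test, if its conditions are met. "Otherwise, the non-parametric Mann-Whitney" U test is used. On the error level it says "In all cases, the level of significance will be the usual 5" per cent.

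The article names no main pain time point, no per-patient summary such as a mean, peak or area under the curve, no repeated-measures method, and no rule for multiple comparisons. It does not say in so many words that each rating will be tested separately.

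**The concern.** Both named tests compare one value per patient between the arms, whereas the schedule produces many values per patient. The text leaves three ways to join the two:

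- test each occasion separately, which gives many chances of a falsely significant result;
- pool all ratings as if they were independent, which would be invalid;
- choose a summary later, which leaves room to choose after seeing the data.

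The first is the most literal reading, since the 5% level is applied to every comparison. At stake is the pain part of the aim. With up to 30 p-values and no stated rule for reading them together, a report could rest a pain claim on a few time points. A reader could not tell how likely that pattern was by chance. Nor would there be one overall estimate of the difference in pain.

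**Working it through.** The plan states no number of pain tests and no overall error rate for them, so there is no figure of its own to reproduce here.

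**Inputs from the protocol article**
- Occasions on the first day: 3 (6, 12 and 24 h).
- Occasions afterwards: 2 per day. Taking the 24 h rating as the end of day 1, days 2 to 7 give 2 × 6 = 12.
- Ratings per occasion: 2, before and after defecation.
- Level per test: 0.05, with no adjustment stated.
- Patients per arm: 72.

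**Assumptions, not in the document**
- Two-sided tests.
- Correlation between a patient's ratings: 0.3 to 0.9.

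**Counts**
- Occasions: 3 + 12 = 15.
- Ratings: 15 × 2 = 30. This is a ceiling, because a patient may not defecate at every occasion.

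**Expected false positives with no true effect**
- 30 × 0.05 = 1.5, and 15 × 0.05 = 0.75. These hold whatever the correlation.

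**Chance of at least one false positive**
- Under independence, 1 − 0.95^k gives 53.7% for k = 15 and 78.5% for k = 30. These are upper reference values only, since one patient's serial pain scores will be correlated.
- Under correlation, the figures come from 4,000 simulated trials per setting, with normal data, 72 per arm, no treatment effect and two-sided t tests:

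| Correlation, equal between all ratings | 15 tests | 30 tests |
|---|---|---|
| 0.3 | 46% | 65% |
| 0.5 | 35% | 51% |
| 0.7 | 26% | 34% |
| 0.9 | 14% | 17% |

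- If correlation instead decays with time between occasions, with 0.7 between the before and after ratings, 30 tests give about 58% (correlation 0.7 between adjacent occasions) or 39% (0.9).

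**Would averaging over the week always be better?** Take an assumed effect of 0.4 SD. The variance of a 15-occasion mean, relative to a single rating, is v = (1 + 14ρ)/15, which is 0.44 for ρ = 0.4 and 0.72 for ρ = 0.7. Power is Φ(effect/√(2v/72) − 1.96).
- One occasion (v = 1): Φ(0.4/0.167 − 1.96) = Φ(0.44) = 67%.
- Mean of 15 occasions, effect constant to day 7: 81% (ρ = 0.7) to 95% (ρ = 0.4).
- Mean of 15 occasions, effect present on only the first 3: the averaged effect is 0.4 × 3/15 = 0.08 SD, and power falls to about 8% (ρ = 0.7) to 11% (ρ = 0.4).

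The gain from averaging therefore depends on how long the effect lasts.

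**The case against.** The strongest reply is that testing at every time point is inferred. The Statistics section names a family of tests and ties it specifically to the baseline comparisons; it nowhere says that VAS will be tested 30 times. A per-patient area under the curve would be compared with exactly the tests it names. A condensed article also commonly leaves the choice of summary to a fuller plan. This stands in part: a missing summary measure alone would be no finding. What remains is that the article does fix the test family and applies the 5% level to every case, and nothing in it limits how many pain comparisons are made under that rule.

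A reader might infer that the named tests do not fit the data because they ignore within-patient correlation. The document does not support that. At one occasion there is one value per patient in two independent arms, and the test holds its nominal 5%. The fault lies in the number of tests and the lack of an overall answer.

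A reader might also infer that the pain comparison is underpowered. That is not established either. The comparison of 67% with 81–95% needs an effect that stays constant to day 7. The arms differ only by one preoperative dose and then follow the same postoperative analgesic scheme, so a fading effect is at least as plausible.

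Finally, pain is a secondary outcome, secondary outcomes are often reported at a nominal 5%, and the plan has no rule that any single significant time point counts as success. This limits the weight of the point but does not remove it, because the aim names the reduction in pain first.

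**Conclusion.** The point holds as one of multiplicity and of a missing single answer. Read literally, the plan allows up to 30 unadjusted pain tests, with 1.5 false positives expected under no effect. The chance of at least one is roughly 17–65% for 30 tests and 14–46% for 15. Those ranges rest on assumed equal correlations of 0.9 to 0.3, two-sided testing and the reading that each rating is tested. Even at a correlation of 0.9, the chance is about three times the nominal 5%. The error rate of the primary outcome, opioid intake, is not affected. The matter should be settled because pain is part of the stated aim, but it does not threaten the trial's primary comparison.

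**What to change.** Before unblinding, state one analysis that will give the VAS result. Either of these would do:

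- a linear mixed model for repeated measures with arm, time, arm-by-time, within-patient correlation, and a term for before or after defecation (or restriction to one named type of rating), reporting the mean arm difference over a stated window;
- one time-averaged area under the curve per patient, for one named type of rating, compared once with the t or Mann-Whitney test already in the plan.

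Fix the averaging window in advance and give the reason for it, since averaging to day 7 would dilute an effect that fades. Present individual time points descriptively with confidence intervals. One such test is carried out at 0.05, whereas a Bonferroni split over 30 tests would leave 0.05/30 = 0.0017 for each.

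The mixed model has a practical advantage. Patients usually go home on day 4 or 5, and the Statistics section itself expects difficulty in collecting data outside the hospital. The model uses whatever ratings each patient has, whereas the area under the curve would need a stated rule for missing ratings.

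The cost is wording in the Statistics section. The schedule already provides for the ratings, and SPSS, the software named, can fit the model. The downside is that isolated time points can no longer be claimed as separate findings.

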### Participant timeline

For the schedule of enrolment, interventions, and assessments, see Table 1.

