**Fig. 1 Fig1:**
[figure not shown]
Trial flow diagram

All relevant data from patient charts except patients’ names will be transferred into an electronic case report form (eCRF). The eCRF should contain results of all the screening procedures, including patient history and demographics, imaging studies, filled-out questionnaires, operation notes, and postoperative rounds during a patient stay in the surgical ward.

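### The text schedules no preoperative VAS pain score or SF-36, yet the ITT definition requires a baseline efficacy evaluation and the secondary comparisons are planned unadjusted

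*Protocol article*

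**What the plan says.** All places are in the protocol article.

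- **Baseline characteristics** gives the items collected to describe the population, run together in the extracted text: "GenderAgeHemorrhoid stageThe number of enlarged hemorrhoidsHemorrhoid symptoms". Neither a VAS score nor the SF-36 is among them.
- **The main outcome measures** times pain as "the pain severity before and after defecation according to VAS on the 6, 12, and 24 h after the procedure", then twice daily to day 7. Quality of life falls under "4) readmission rate and (5) overall quality of life on the 7th and 30th days". The instrument is named ("The overall quality of life will be assessed with a patient-reported questionnaire Short Form 36 (SF-36") and its 0–100 scoring described, but no version or recall period is given.
- **Statistics** defines the ITT set as randomised patients treated for at least a week "who were evaluated for efficacy at baseline and at least once at subsequent evaluation points during the study". Quantitative variables are compared with a t test or, failing its conditions, a Mann-Whitney test. No baseline covariate or change score is mentioned.
- **Participant timeline** refers the reader elsewhere: "For the schedule of enrolment, interventions, and assessments, see Table 1". The body of that table is not shown. Its visible footnotes define three follow-ups, all postoperative.

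**The concern.** Two things do not fit together. Every time stated for pain and quality of life is after surgery, while entry to the ITT set depends on an efficacy evaluation before it. Read literally, a randomised patient could be left out of the main analysis, including that of opioid intake, for want of an assessment the text never schedules.

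The second matter is efficiency. Lower postoperative VAS pain is the first-named aim under Objective, and all patients enter with symptomatic disease, so they plausibly differ in pain and quality of life before the tablet. Without a preoperative score, that variation stays in the error term of the secondary comparisons. The planned check of whether randomisation worked also cannot cover the two scales on which efficacy is later judged.

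The meaning of the day-7 SF-36 further depends on a recall period that is not stated.

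**Working it through.** The article gives no figure on this point, so there is none to reproduce.

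**Step 1. Timing of each measure, as stated in the text**

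| Measure | Preoperative | Postoperative |
|---|---|---|
| VAS pain | none described | 6, 12, 24 h, then twice daily to day 7 |
| SF-36 | none described | days 7 and 30 |
| ITT condition | baseline efficacy evaluation required | at least one later evaluation |

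The third row needs an entry that the first two do not supply.

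**Step 2. Precision forgone without adjustment**

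Inputs: 72 patients per arm (Sample size); 5% significance (Statistics), taken as two-sided; 80% power, used here only as a yardstick for the secondary scores. The baseline-outcome correlation r is an assumption, because the documents give none. The range 0.2 to 0.6 is used, its low end to allow for pain soon after excision being only weakly related to preoperative pain.

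Residual variance after adjustment, as a share of the unadjusted variance, is 1 − r². The detectable standardised difference is (1.960 + 0.842) × √(2/72 × (1 − r²)).

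| r | 1 − r² | Variance cut | Equivalent patients per arm, 72/(1 − r²) | Detectable difference |
|---|---|---|---|---|
| 0 | 1.00 | 0% | 72 | 0.467 |
| 0.2 | 0.96 | 4% | 75 | 0.457 |
| 0.4 | 0.84 | 16% | 85.7 | 0.428 |
| 0.6 | 0.64 | 36% | 112.5 | 0.374 |

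**Step 3. Share of the day-7 SF-36 window that lies before surgery**

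For an assumed recall of R days the share is max(0, R − 7)/R.

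- R = 7: 0/7 = 0%
- R = 14: 7/14 = 50%
- R = 28: 21/28 = 75%

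At day 30 the share is 0% for all three lengths.

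**The case against.** The strongest reply is that a baseline assessment may well exist. Table 1, where it would naturally appear, is not shown. The paragraph after Fig. 1 says "The eCRF should contain results of all the screening procedures, including patient history and demographics, imaging studies, filled-out questionnaires", which could include a preoperative SF-36. The ITT wording itself suggests that some baseline evaluation was intended, and the listed hemorrhoid symptoms may cover pain in some form. This stands. A reader might infer that pain and quality of life have no baseline at all, but the documents shown cannot establish that. They support only the statement that the text describes none.

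A reader might also infer that the day-7 SF-36 mostly reflects life before surgery. That holds under a 28-day recall, is exactly half under 14 days and is false under 7 days. With no recall period given, it can be said only conditionally.

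Thirdly, a missing baseline might be taken to bias the results. It does not: the randomised contrast of postoperative scores remains valid, and opioid intake has no such preoperative score to miss. The size of the precision gain also rests wholly on assumed correlations. At r = 0.2, plausible for early pain after excision, the gain is small.

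Finally, covariate adjustment and questionnaire versions are often left to an analysis plan or full protocol, neither of which is shown. That is fair for those details taken alone. It does not remove the conflict between the ITT definition and the stated assessment times, and an analysis plan cannot adjust for a score that was never collected.

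**Conclusion.** The point holds in a limited form. The firm part is the inconsistency: Statistics makes ITT membership depend on a baseline efficacy evaluation that neither Baseline characteristics nor The main outcome measures provides. It rests on no assumption beyond the text, and it could reach the primary analysis through the choice of patients.

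The rest concerns secondary outcomes and is a matter of efficiency and interpretation. For correlations of 0.2 to 0.6, the planned unadjusted tests forgo a 4% to 36% reduction in residual variance, and the check of baseline balance cannot include the two scales. If Table 1 does contain a baseline score, using it as a covariate is free. If it does not, collecting it is cheap. The recall issue amounts to a request to name the version, because the preoperative share of the day-7 window runs from 0% to 75% according to that choice.

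**What to change.** 1. In Statistics, remove the baseline-efficacy condition from the ITT definition, or reconcile it with Baseline characteristics and The main outcome measures, so that no randomised patient drops out of the primary analysis for lack of an unscheduled assessment.
2. In Baseline characteristics and The main outcome measures, state that VAS pain and SF-36 are completed after consent and before randomisation and the study tablet. Consent already precedes randomisation under Eligibility criteria, so the time point exists. If Table 1 already schedules these scores, say so in the text.
3. Compare later VAS and SF-36 scores with the matching baseline as covariate, by ANCOVA or a repeated-measures model.
4. Name the SF-36 version and its recall period. If the recall is longer than one week, use a one-week form on day 7 and for the matching baseline.

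The cost is a few minutes per patient for one VAS mark and one questionnaire. The real limit is timing. Trial status expects recruitment to run from April 2020 to the end of December 2021, so patients already enrolled may lack the score and the adjusted analysis would have to say how they are kept in. Item 1 and the naming of the version in item 4 are changes of wording and can be made however far recruitment has gone.
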